### Ethical Considerations

Participants are asked about suicidality at all measurement time points (T1, T2, and T3). For safety reasons, subjects will be contacted if they report suicidal thoughts and an emergency plan is drawn up with them. Nevertheless, the subject’s data will not be passed on to the police or other authorities. If participants endorse suicidality, they will be excluded from further data analyses, and only the assessments up to the occurrence of suicidality will be used.

The study center at the University of Giessen is responsible for storing and analyzing patient data. Besides the initial interview, all data are collected via a web-based platform (SoSci Survey; SoSci Survey GmbH) that uses SSL encoding to protect the data and stores them on servers located in Germany. Participant data are stored pseudonymously in order to access contact data in cases of suicidality. However, after the study is finished, the data will be immediately deidentified. Written informed consent is obtained from all participants before participation, and the ethics committee of the Faculty of Behavioral and Empirical Cultural Science at the study center at Heidelberg University approved the clinical protocol (AZ [name] 2021 1/1). The trial is registered at the German Clinical Trials Register (DRKS00023800) and follows the ethical principles of the Declaration of Helsinki. All patients receive an allowance of €30 (US $33) after completing the study.

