## Methods

### Participants

Recruitment is carried out through newsletters and social media advertising drawing attention to Selfapy. Interested individuals can register for participation on the web, and after a successful video call–based screening procedure they will be contacted by the study center to schedule a diagnostic appointment.

Video calls will be conducted with all subjects, during which eligibility will be evaluated based on a diagnostic interview, the Diagnostic Interview for Mental Disorders–Open Access (DIPS-OA) [26]. Trained interviewers with at least a master’s degree (or equivalent) in psychology focusing on clinical psychology will conduct all interviews. The interviewers are trained at the Justus Liebig University in Giessen, Germany. Furthermore, there is close supervision on questions of diagnostics, as well as the inclusion and exclusion criteria, by a psychotherapist licensed in CBT.

Eligible subjects (1) are aged between 18 and 65 years, (2) have sufficient knowledge of the German language, (3) have uninterrupted internet access, (4) provide electronic informed consent to participate in the study, and (5) currently meet the diagnostic criteria according to the Diagnostic and Statistical Manual of Mental Disorders [1] for a diagnosis of GAD (International Classification of Diseases, 10th Revision code F41.1).

Subjects will be excluded if they do not fulfill any of the inclusion criteria or meet any of the following exclusion criteria: (1) past or current diagnosis of bipolar disorder, (2) past or current diagnosis of psychotic disorder, (3) current diagnosis of substance dependence, (4) current diagnosis of a severe major depressive episode, and (5) acute suicidality. A primary diagnosis of a disorder other than GAD is not an exclusion criterion, as we want to represent routine care. However, substance dependence, bipolar disorder, or psychotic illness are exclusion criteria because they conflict with the implementation of the program. Subjects who do not meet our inclusion criteria due to severity of illness are encouraged to seek professional help. Adequate language skills will be determined during the initial interview.

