### Statistical Analyses

For the psychometric outcome analyses, all patients who were randomly assigned to the 2 conditions and completed the initial survey (T1) will be included in an intention-to-treat (ITT) analysis. All available data will be used for this purpose. Missing values in the data will be replaced by multiple imputations (multivariate imputation by chained equations with n=5 imputations) based on the control arm, using the variables “age” and “gender” as predictors in addition to the measurement-repeated stress indicators. In addition, last-observation-carried-forward, baseline-observation-carried- forward, reference-based-multiple imputation (jump-to-reference approach [49]), and completer sensitivity analyses will be performed.

The confirmatory analysis of the primary outcomes consists of calculating a mixed model with 2 measurement time points and a general correlation structure [47]. A random effect for the subjects is calculated (random intercept) and 3 fixed effects (group assignment, time, and the interaction of the 2 predictors). The 2 measurement time points are nested within subjects. The primary outcomes will be evaluated using a Bonferroni-Holm correction for α error inflation. Secondary confirmatory outcomes will only be analyzed if the results of the primary analysis confirm the hypotheses, and the same mixed model with a random intercept for the subject will be applied. Again, a Bonferroni-Holm correction will be used.

Independent 2-tailed *t* tests and chi-squared tests will be used to estimate differences between groups in pretreatment sample characteristics. In addition to the ITT sample, a “per-protocol” sample sensitivity analysis is defined for exploratory analyses, including all patients in the intervention group who completed at least 4 of the modules.

There are different approaches to calculating effect sizes for mixed modeling data in the literature [50]. Hedges [50] and Westfall et al [51] propose an effect size based on the Cohen *d*, which is also used for power analysis [47]:

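### Discarding assessments after a participant endorses suicidality conflicts with the all-available-data ITT rule and can bias the T3 comparison in either direction

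*Protocol article*

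**What the plan says.** Two sections of the protocol article govern the same data.

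- **Ethical Considerations.** Suicidality is asked about at T1, T2 and T3. Participants reporting suicidal thoughts are contacted and an emergency plan is made. The section then sets an analysis rule: "If participants endorse suicidality, they will be excluded from further data analyses", and "only the assessments up to the occurrence of suicidality will be used".
- **Statistical Analyses.** The population is defined as "all patients who were randomly assigned to the 2 conditions and completed the initial survey (T1) will be included in an intention-to-treat (ITT) analysis". The data rule follows at once: "All available data will be used for this purpose". For gaps, "Missing values in the data will be replaced by multiple imputations", five in number and based on the control arm. Sensitivity analyses are last observation carried forward, baseline observation carried forward, jump-to-reference imputation and completers, plus an exploratory per-protocol sample.

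The Statistical Analyses section makes no exception for suicidality. The Ethical Considerations section gives no statistical reason for its rule. Acute suicidality is already an exclusion criterion at entry (Participants), and the primary outcomes are the GAD-7 and WHO-5 at T3.

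**The concern.** The exclusion is triggered by something that happens to the participant. At T2 and T3 that event comes after randomisation. It is likely to go with worse anxiety, mood and well-being, and its frequency may differ between arms. Detection may differ too. Study Design describes a psychologist who monitors progress in the programme and responds to suicidality, while waitlist patients get no support from the researchers for 12 weeks. The article does not say whether suicidality noticed through that monitoring counts as endorsement.

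Dropping observed outcomes after such an event removes poor scores selectively and gives up part of the protection that randomisation provides. The values put in their place come from a control-arm model. The rule covers every outcome, including the Negative Effects Questionnaire at later visits. At stake are the T3 estimate for both primary outcomes and, to a lesser degree, power.

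**Working it through.** **1. The two rules applied to the same participant**

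| Endorses at | Ethical Considerations | Statistical Analyses |
|---|---|---|
| T2, then completes T3 | T1 kept, T2 unclear, T3 dropped | T1, T2 and T3 all used |
| T3 | T1 and T2 kept, T3 unclear | T1, T2 and T3 all used |

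The unclear cells arise because the article does not say whether the visit at which suicidality is endorsed is itself kept. That decides whether T3 endorsers lose their primary outcome. On either reading, the T2 endorser's observed T3 value is discarded.

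**2. Can a planned analysis recover the value?** No. Multiple imputation and jump-to-reference replace it, the two carry-forward methods substitute an earlier score, and the completer analysis omits the person.

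**3. The plan's own sample size.** Inputs from Power and Sample Size: d = 0.45, directed hypothesis, α = 0.025, power 0.80, 1:1 allocation.

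- n per arm = 2(1.960 + 0.842)²/0.45² = 77.5, so 78 per arm and 156 in total, as stated.
- Power at 78 per arm = Φ(0.45·√(78/2) − 1.960) = Φ(0.850) = 0.802.

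**4. Power after losing T3 values.** The counts are assumed and split evenly between arms. Imputed values are taken to add no information.

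| T3 values lost | Left per arm | Power |
|---|---|---|
| 4 | 76 | 0.792 |
| 8 | 74 | 0.782 |
| 16 | 70 | 0.759 |

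**5. Direction of bias.** Let pC and pI be the shares of each arm whose T3 value is discarded, and g the number of SDs by which discarded scores are worse than their replacements. Then

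apparent benefit = 0.45 − pC·g + pI·g.

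With g = 1:

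- 5% control, 10% intervention (about 4 and 8 of 78): 0.45 − 0.05 + 0.10 = 0.50.
- 10% control, 5% intervention: 0.45 − 0.10 + 0.05 = 0.40.
- 5% in both arms: 0.45, no bias.

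With g = 0.5 the two unequal cases give 0.475 and 0.425.

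**6. Simulation.** Assumptions: 1,000,000 per arm, SD 1, correlation 0.5 between visits, true differences of 0.225 SD at T2 and 0.45 SD at T3. Endorsement is more likely with a worse current score, at 3% to 15% per visit in the control arm.

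| Who loses T3 | Completers | Control-based imputation |
|---|---|---|
| T2 endorsers only | 0.44 to 0.45 | 0.39 to 0.44 |
| T2 and T3 endorsers | 0.39 to 0.44 | 0.33 to 0.43 |

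Discarded T3 scores were worse than their own arm's mean in every scenario (by 0.23 to 1.00 SD in the control arm). When only T2 endorsers lost T3 and imputation used T1 and T2 within arm, the bias was about zero (0.45).

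**The case against.** The strongest reply is that endorsers are not removed from the ITT set. Their assessments up to the event remain, and every randomised patient with T1 is in the population. This stands. A reader might infer that the rule breaks the ITT population, but the conflict is with the instruction to use all available data.

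Three further replies also have force.

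- **Size.** The document gives no endorsement rate, and the entry exclusions for acute suicidality and severe depressive episodes should keep it low. If the endorsing visit is kept, only earlier endorsers lose T3. In that case much of the simulated attenuation comes from imputing on the control arm, which is a separate choice.
- **Later data.** The article does not say that questionnaires continue after endorsement. If they stop, there is nothing to discard. The rule excludes from analysis, however, and does not say that participants leave the study.
- **Harms.** A reader might infer that a harm signal would be hidden. The documents do not support that: suicidality is asked about in both arms at every visit and can still be counted by arm.

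A reader might also infer that anyone with non-acute suicidal thoughts at T1 is randomised and then contributes no follow-up. The article does not define endorsement or tie it to such thoughts. T1 also precedes randomisation, so endorsement there is a baseline characteristic and not an effect of treatment.

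None of this removes the clash between the two sections or supplies an analysis that uses the discarded values.

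**Conclusion.** Wrong as written. The two sections give incompatible instructions for data observed after endorsement. Following the Ethical Considerations rule drops outcome values because of an event that follows randomisation and is likely to be related to severity.

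The bias can favour either arm, and its size cannot be determined from the document. It is small if endorsement is rare. The illustrative shift of 0.05 SD either way is 11% of the design effect (0.05/0.45). It rests on assumed rates of 5% and 10% and an assumed 1 SD gap between discarded scores and their replacements. The power loss, to between 0.79 and 0.76, rests on assumed losses of 4 to 16 T3 values. A stronger conclusion, that the rule would erase a treatment effect or a harm, would need high and unequal endorsement rates that nothing in the document supports.

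Whether the endorsing visit is kept is a gap of its own, because it determines how many primary outcomes are lost.

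**What to change.** Delete the analysis exclusion in Ethical Considerations. In its place, state that all assessments collected at and after endorsement of suicidality stay in the ITT analysis of every outcome. Values that were never collected are then handled by the missing-data rule like any others. Report the number of participants endorsing suicidality by arm and visit.

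This costs one sentence of wording and a small table. The sample size stays at 156, and the rule no longer costs any T3 values. The safety contact and emergency plan are unchanged. The Results section says that participants had finished and the report was in preparation, so the change affects only the analysis, and any departure from the published rule should be declared in the report.

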### Hypotheses

The main objective of this trial is to determine the efficacy of the 12-week Selfapy course for patients with GAD compared to a wait-list control group. Additional outcome data will be collected at 6 weeks. However, our confirmatory hypotheses, which will evaluate a positive health care effect, will focus on the 12-week outcomes. The following 2 hypotheses refer to our primary outcomes:

GAD symptomatology (measured with the GAD-7 [27]) will significantly decrease with the use of the Selfapy course for GAD after 12 weeks compared to a wait-list control group.Perceived quality of life (measured with the WHO-5 [28]) will significantly increase after 12 weeks of the Selfapy course for GAD compared to a wait-list control group.

The following secondary outcomes will only be analyzed if the hypotheses for the primary outcomes are confirmed. They will also be tested using Bonferroni-Holm adjustment:

Difficulties in daily life (measured with the WSAS [30]) will significantly decrease after using the Selfapy course for GAD after 12 weeks compared to a wait-list control group.Using the Selfapy course for GAD will lead to significantly better recovery of working ability (measured with the iPCQ [32]) after 12 weeks compared to a wait-list control group.Health literacy (measured with the MHLS [34]) will significantly improve with the use of the Selfapy course for GAD after 12 weeks compared to a wait-list control group.The extent of therapy-related efforts and burdens of patients and their relatives (measured with the CSSRI [35]) will be significantly reduced after using the Selfapy course for GAD compared to a wait-list control group after 12 weeks.

Our exploratory hypotheses do not address the target symptoms and are therefore not adjusted for α accumulation:

Worry symptoms (measured with the PSWQ [36]) will significantly decrease with the use of the Selfapy course for GAD after 12 weeks compared to a wait-list control group.Self-rated anxiety symptoms (measured with the BAI [39]) will significantly decrease with the use of the Selfapy course for GAD after 12 weeks compared to a wait-list control group.Self-rated depressive symptoms (measured with the PHQ-9 [41]) will significantly decrease with the use of the Selfapy course for GAD after 12 weeks compared to a wait-list control group.The Selfapy course for GAD will not lead to any side effects compared to a wait-list control group after 12 weeks (measured with the NEQ [42]).

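### The suicidality rule, as worded, discards the observed 12-week scores of eligible, randomised patients who reported non-acute suicidality at baseline

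*Protocol article*

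**What the plan says.** Under Ethical Considerations, the protocol article states: "Participants are asked about suicidality at all measurement time points (T1, T2, and T3"). On safety, "subjects will be contacted if they report suicidal thoughts and an emergency plan is drawn up with them". On the data, "If participants endorse suicidality, they will be excluded from further data analyses, and only the assessments up to the occurrence of suicidality" are to be used.

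Under Participants, the last two exclusion criteria read "4) current diagnosis of a severe major depressive episode, and (5) acute suicidality". Suicidality that is not acute does not bar entry.

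Under Study Design, and again under Randomization and Blinding, the entry questionnaire (T1) comes before random assignment.

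Under Hypotheses, "our confirmatory hypotheses, which will evaluate a positive health care effect, will focus on the 12-week outcomes"; the two primary outcomes are the GAD-7 and the WHO-5.

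Under Statistical Analyses, "all patients who were randomly assigned to the 2 conditions and completed the initial survey (T1) will be included" in the intention-to-treat analysis, and "All available data will be used for this purpose". The same paragraph adds: "Missing values in the data will be replaced by multiple imputations (multivariate imputation by chained equations with n=5 imputations) based on the control arm". A completer analysis is among the sensitivity analyses.

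**The concern.** The safety question is put at T1, before randomisation, to patients who have already passed the diagnostic interview. Some of them may report suicidality that is not acute. They are eligible and will be randomised, yet the data rule in Ethical Considerations applies to them from T1 onwards.

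For such a patient two stated rules cannot both be followed. One keeps every randomised patient with a T1 survey in the analysis and uses all data available. The other stops using the patient's data after T1. If the second prevails, real 12-week scores on both confirmatory outcomes are thrown away. Nothing about patient safety requires this, because the contact and emergency plan work without it.

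At stake is either some dilution of the estimated effect, if the scores are replaced by control-based imputations, or some loss of precision and a departure from intention to treat, if the patient is left out of the T3 comparison.

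**Working it through.** **Step 1: what happens to one patient.** Take a patient with non-acute suicidality at T1.

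| Stage | Section | Consequence |
|---|---|---|
| Eligibility | Participants | Not excluded: only acute suicidality bars entry |
| T1 survey, then randomisation | Study Design | Endorsement recorded, then randomised |
| Analysis set | Statistical Analyses | In the intention-to-treat set |
| Data used, general rule | Statistical Analyses | T1, T2 and T3 |
| Data used, suicidality rule | Ethical Considerations | T1 only |

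The last two rows conflict. What happens to the T3 score after that is not stated. There are two possibilities: (a) it counts as a missing value and is imputed, or (b) the patient is absent from the T3 comparison.

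**Step 2: reproduce the planned sample size.** Inputs from Power and Sample Size: d = 0.45, a directed hypothesis, α = .025, power 0.80, allocation 1:1.

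n per group = 2 × (1.960 + 0.842)² / 0.45² = 77.5, rounded up to 78, or 156 in total. This matches the article. The power at that size is Φ(0.45 × √(156/4) − 1.960) = 0.802.

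**Step 3: size of the consequence.** Let p be the share of randomised patients who endorse non-acute suicidality at T1. The article gives no value, so 2%, 5% and 10% are assumptions.

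- *Left out (b):* N = 156 × (1 − p), power = Φ(0.45 × √(N/4) − 1.960).
- *Imputed (a), taking the imputed values to carry no treatment effect:* d = 0.45 × (1 − p), power = Φ(d × √(156/4) − 1.960).

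| p (assumed) | Patients affected (p × 156) | N if left out | Power if left out | d if imputed | Power if imputed |
|---|---|---|---|---|---|
| 0 | 0 | 156 | 0.80 | 0.450 | 0.80 |
| 2% | about 3 | 153 | 0.795 | 0.441 | 0.786 |
| 5% | about 8 | 148 | 0.78 | 0.428 | 0.76 |
| 10% | about 16 | 140 | 0.76 | 0.405 | 0.72 |

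These use the same two-group formula that reproduces the planned 78. They give an order of magnitude and do not recompute the mixed model. A fuller simulation would also need an assumed T1–T3 correlation and a choice of whether d is scaled to the T3 score or to the change score. The article fixes neither in a way that would sharpen the figures.

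**The case against.** The strongest reply is that the rule was never meant for baseline. Stopping at the occurrence of suicidality sounds like an event during follow-up. Baseline has its own rule in the eligibility criteria, and assignment happens only if those are met. The article also uses two terms: suicidal thoughts trigger contact, and suicidality triggers exclusion from analysis. If the second means acute suicidality, no eligible patient is affected at T1. This reading is coherent and may be what was intended. It is not what is written: suicidality is undefined in that section, T1 is named among the time points, and the word *acute* appears in the exclusion criteria but not in the data rule.

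A second reply is that a specific safety provision qualifies the general commitment to use all data. That could settle which rule takes precedence, but it gives no reason to discard the scores.

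A reader might infer three stronger things, and the documents support none of them:

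- *That the plan imputes these scores from the control arm.* This is one possible consequence. The suicidality rule does not say that discarded scores become missing values. Jump-to-reference imputation is listed separately as a sensitivity analysis, so it is also unclear whether the main imputation gives intervention patients control-like outcomes. The dilution column is therefore a pessimistic case.
- *That the comparison is biased by an imbalance between arms.* Endorsement at T1 precedes allocation, so the loss is balanced in expectation. Endorsement at T2 could depend on treatment, but that is a separate question and is not assessed here.
- *That the trial lost a known amount of power.* No endorsement rate is given, and severe depressive episodes and acute suicidality are screened out, so the number could be small.

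**Conclusion.** The point holds as a conflict between two stated rules. As worded, collected T3 GAD-7 and WHO-5 scores of eligible, randomised patients are discarded because of something reported before allocation, contrary to the intention-to-treat rule and the use of all available data.

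The likely size is modest and cannot be fixed from the article. If 2% of patients were affected the cost would be negligible. At 5% power would be about 0.76–0.78, and at 10% about 0.72–0.76, against 0.80 planned. In each range the upper figure applies if the patients are left out, and the lower if their scores are replaced by values carrying no treatment effect. Besides the assumed rates, the figures rest on the simple two-group formula. If only acute or newly arising suicidality was meant, nobody is affected at T1 and the matter reduces to a clarification. Either way the text should say so, because an analyst following it literally would delete confirmatory data.

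**What to change.** Add one sentence to the data rule in Ethical Considerations, along these lines: *A patient who reports suicidality at T1 but does not meet exclusion criterion 5 receives the safety contact and emergency plan and is not removed from analysis; every T2 and T3 score collected from such a patient enters the intention-to-treat analysis.*

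No new data are needed and the safety procedure is unchanged, since the sentence affects only which collected scores are analysed. The cost is one of transparency. The article reports that all participants had finished by May 2023, so this alters a published rule after data collection and must be disclosed as such. Ideally it is made before the group codes are opened; the article plans a blinded analysis but does not show whether the codes are still closed. If they are not, report the result under the amended rule alongside the result under the rule as published, with the number of patients affected in each arm.
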